## Abstract

**Background:**

Opioid overdose is a global health crisis, affecting over 27 million individuals worldwide, with more than 100,000 drug overdose deaths in the United States in 2022-2023. This protocol outlines the development of the PneumoWave chest biosensor, a wearable device being designed to detect respiratory depression in real time through chest motion measurement, intending to enhance early intervention and thereby reduce fatalities.

**Objective:**

The study aims to (1) differentiate opioid-induced respiratory depression (OIRD) from nonfatal opioid use patterns to develop and refine an overdose detection algorithm and (2) examine participants’ acceptability of the chest biosensor.

**Methods:**

The study adopts an observational design over a 6-month period. The biosensor, a small device, will be worn by consenting participants during injecting events to capture chest motion data. Safe injecting facilities (SIF) in Melbourne, Victoria (site 1), and Sydney, New South Wales (site 2), which are legally sanctioned spaces where individuals can use preobtained illicit drugs under medical supervision. Each site is anticipated to recruit up to 100 participants who inject opioids and attend the SIF. Participants will wear the biosensor during supervised injecting events at both sites. The biosensor will attempt to capture data on an anticipated 40 adverse drug events. The biosensor’s ability to detect OIRD will be compared to the staff-identified events that use standard protocols for managing overdoses. Measurements will include (1) chest wall movement measured by the biosensor, securely streamed to a cloud, and analyzed to refine an overdose detection algorithm and (2) acute events or potential overdose identified by site staff. Acceptability will be measured by a feedback questionnaire as many times as the participant is willing to throughout the study.

**Results:**

As of April 2024, a total of 47 participants have been enrolled and data from 1145 injecting events have already been collected, including 10 overdose events. This consists of 17 females and 30 males with an average age of 45 years. Data analysis is ongoing.

**Conclusions:**

This protocol establishes a foundation for advancing wearable technology in opioid overdose prevention within SIFs. The study will provide chest wall movement data and associated overdose data that will be used to train an algorithm that allows the biosensor to detect an overdose. The study will contribute crucial insights into OIRD, emphasizing the biosensor’s potential step forward in real-time intervention strategies.

**International Registered Report Identifier (IRRID):**

DERR1-10.2196/57367

## Introduction

Worldwide, more than 27 million people have an opioid use disorder and more than 150,000 people die each year from opioid overdose [1,2]. In the United States, in 2022-2023, there are estimated to be more than 100,000 drug overdose deaths [3]. Naloxone is an opioid antagonist and an antidote to opioid overdose. Effective interventions, such as take-home naloxone are available [4,5] but coverage is incomplete and they are not suited to many overdose situations, such as when people may be alone or the onset of their overdose goes unnoticed [6-8]. In such situations, intervention requires detection of the overdose to signal the need for a response.

Recently, technological developments in wireless “wearable” devices have enabled real-world, real-time measurement of physiological functioning and these devices have grown hugely in popularity [9-11]. Devices in relation to overdose could capture a wide range of different parameters but it is important that these are sensitive, accurate, and reliable. Opioids affect the control of breathing and can cause fatal overdoses, usually by respiratory failure. Respiratory depression, referring to the characteristic effect of opioid drugs, is slowed and shallow breathing (or reduced chest movement) which can sometimes lead to changes in levels of blood gasses and a suppression of the usual responses to these changes. This can lead to hypoxia, respiratory failure, and death. However, currently available wearable devices lack the ability to analyze and interpret respiratory depression data in real time and with sufficient accuracy to achieve medical device regulatory clearance. They are also not practical or economically viable for individual use in the community [12]. A chest sensor that reliably detects the overdose breathing signature, in real time, could alert family or friends to help or could directly alert emergency service. This could save lives when fully developed and used in the community.

The PneumoWave chest biosensor is a small device (Figure 1; 40 mm in diameter and 14 mm in height) that sticks onto the chest using a small plastic patch (an [electrocardiographic] ECG sticker). The device measures chest motion, and consequently will be able to detect changes in chest movement. However, to be relevant to the detection of overdoses in the community, research is required on people at high risk of opioid-induced respiratory depression (OIRD) to capture chest motion during an injecting event, where the absence or presence of overdose can be externally verified. This will then be used to develop and refine sensitive and specific OIRD detection algorithms that can interpret chest movement data in real time on a smartphone or tablet without the need for live clinician analysis and interpretation.

**Figure 1 figure1:**
[figure not shown]
Image of PneumoWave chest sensor and location of placement on the body.

Those who inject opioids die at a much higher rate than other drug-using groups [13]. A safe injecting facility (SIF), also known as a medically supervised injecting center or room, drug consumption room, safe consumption room, or overdose prevention center, is a legally sanctioned space where people can bring their own preobtained illegal or illicit drugs, and either inject or inhale them using sterile equipment under the supervision of nurses or other medical professionals. The main objective of a SIF is to improve survival and increase social integration [14]. However, overdoses, while at a lower rate than the general using population, still occur at SIFs [15]. This also provides an important opportunity for study [16].

In this study, as participants wear the biosensor while they are injecting their opioids, the objectives of the study are (1) to capture chest motion data using the PneumoWave biosensor, and staff-measured outcomes as the clinical reference (including clinical identification of an acute event), during instances of opioid injection and potential opioid overdose by attendees at a SIF, to develop and refine the overdose detection algorithm and (2) to examine acceptability to SIF attendees of the chest biosensor.

## Methods

### Ethical Considerations

This paper is based on version 1.1, April 5, 2023, of the study protocol. Ethics was approved by the Alfred Hospital Ethics Committee (92786). This study adheres to the Standard Protocol Items: Recommendations for Interventional Trials (SPIRIT) checklist (Multimedia Appendix 1).

In order to obtain informed consent, the site research personnel will explain the study methodology to the potential participant, the individual will be given time to read the participant information sheet and consider participation, and if they agree to participate, informed consent will be obtained. Study explanation can occur before or after using the SIF, depending on the preference of the client and aligning with the capacity to consent. Study enrollment and first recording injecting events can, therefore, occur on different days.

Data will be recorded pseudo-anonymously (ie, pseudonyms will be used; no personally identifiable information will be stored alongside chest motion data) and streamed to a secure cloud. Participants who consent to take part will be assigned a numerical study ID number that will be linked to subsequent visits that they make to the Medically Supervised Injecting Centre (MSIC) or Medically Supervised Injecting Room (MSIR). All electronic data will be anonymous and stored on secure, password-protected devices or servers, accessible only by approved study personnel. All paper-based consent forms containing participant names will be kept on site at the MSIC or MSIR following completion and will not be removed from the site.

To reimburse participants for their time and inconvenience, participants will be reimbursed Aus $50 (US $33.20) following initial screening and study enrollment. Participants will then receive a weekly reimbursement of Aus $20 (US $13.30) on the basis they have attended the MSIC or MSIR to inject opioids (either alone or in combination with other drugs) while wearing the biosensor device at least once during the week.

### Objectives

The objectives of the study are (1) to capture chest motion data using the PneumoWave biosensor, and staff-measured outcomes as the clinical reference (including clinical identification of an acute event), during instances of opioid injection and potential opioid overdose by attendees at a SIF, to develop and refine the overdose detection algorithm and (2) to examine acceptability to SIF attendees of the chest biosensor.

### Study Design

This is an observational pilot study. Over 6 months, this study aims to capture approximately 40 overdose events that occur for consenting participants who are wearing the chest sensor during visits to inject at the SIF. Participants who consent to take part will be assigned an anonymous, numerical study ID number that will be linked to subsequent visits that they make to the SIF.

Chest motion data will be collected on the device securely and pseudo-anonymously (ie, pseudonyms will be used; no personally identifiable information will be stored alongside chest motion data) and streamed to a secure cloud. A SIF is designed to respond to a broad spectrum of adverse drug reactions, recognizing that not all incidents may escalate to an opioid overdose (thus any event that is attended to and requires prompting by staff is termed an “acute event”). The data collected here will be used to test and further develop chest wall movement “signatures” to accurately detect an “acute” drug event or potential overdose, as diagnosed by the current clinical observations in the SIFs. Wearing the device will not alter the services participants receive at the SIF and the sites will manage each acute event as per their standard protocols.

### PneumoWave Biosensor and Data Collection Platform

The study will use the PneumoWave biosensor and data collection platform, which includes a wearable biosensor that attaches to the press-stud on a supplied and approved ECG electrode. The biosensor can be placed in a number of locations on the chest and diaphragm area and automatically connects to a Data Hub via Bluetooth (Figure 1). In this study, the Hub will be a router-type device or a mobile computing platform (app running on a tablet or phone).

Once consented to and enrolled in the study, participants will be asked to wear the biosensor each time they attend their relevant SIF to take opioids, an unlimited number of times. There will be no predefined number of visits that each participant should adhere to, though reimbursement will be predicated on attendance to the SIF and wearing of the biosensor at least weekly. We will now highlight the inclusion and exclusion criteria applicable to the study.

### Eligibility Criteria

#### Inclusion Criteria

Participants will be recruited from the SIFs via advertisement and direct approach by site personnel and must meet the criteria that are (1) be an adult (18 years of age or older), (2) current injecting opioid user (note: participant may be using other substances as well), (3) regular client of the SIF (minimum of 4 visits in the past month), and (4) willingness to wear biosensor device while injecting at the facility.

#### Exclusion Criteria

The exclusion criteria are (1) inability to provide informed consent, (2) younger than 18 years of age, (3) not currently injecting opioids, (4) skin sensitivity to ECG electrodes, (5) broken skin over the chest area, (6) implanted pacemaker device in situ, and (7) in the clinical opinion of the investigator would not be suitable to participate.

### Sample Size

Participants will be recruited via purposive selection—SIF staff will identify individuals who frequently attend the SIF and inject opioids—and via site advertisements, with individuals approaching site research personnel about potential participation.

During a study period of 6 months, we estimate that approximately 100 participants will be recruited at each participating SIF to meet the desired targets of approximately 2000 opioid injecting visits (a total of 4000 visits), leading to approximately 40 recorded acute or overdose events. This is based on an estimated overdose event rate (the proportion of injections that result in an overdose event) to be 1.2%, from previous data from the medically supervised injecting center in Sydney, New South Wales, Australia [15,17]). An estimated 1200 opioid injecting visits occur per month per site, with an estimated 70 unique individuals attending for opioid injecting per month, per site.

### Outcome Measures

#### Overview

We will initially separate outcome measures into categories of primary outcome measures (chest motion measures and acceptability) and SIF-determined measures. The latter will then be separated into intervention measures and acute event measures.

#### Primary Outcome Measures

Capture of chest motion of participants includes chest wall measurements via PneumoWave biosensor of people before and after injection of opioids in a SIF, compared by (1) those experiencing hypoxia and meeting defined criteria for an acute or opioid overdose (SIF-determined outcome measure or acute event) and (2) those not experiencing symptoms of hypoxia or acute or opioid overdose (ie, safe injecting event).

#### SIF-Determined Outcome Measures

The data that will be collected for each opioid injecting event in the SIF are (1) participant study ID, (2) time or date of client presentation to SIF, (3) substances reported by the participant as intended for injecting (confirmation that opioids are being injected), (4) time of opioid use, and (5) any apnea and prompts to breathe.

The outcome data that will be recorded for any intervention by SIF clinical staff (including acute event response) are (1) precise timing of the first clinical indication of acute event, (2) unique ID number of clinician initially assessing the event to be an opioid overdose, and (3) opioid overdose criteria being met (based on-site specific training materials or opioid overdose reference criteria). These are based on the measures that are described next.

The outcome measures that will be collected for each acute event (including prompts), as applicable are (1) response to audio, physical, and painful stimuli; (2) level of consciousness—timepoints as per standard of care, recorded (using Alert Verbal Pain Unresponsive [AVPU] scale—see Multimedia Appendix 2) at intervals indicated by clinical concern; (3) respiratory rate recorded at least every 5 minutes (though in practice, likely more often) after first clinical indication of opioid overdose; (4) heart rate—timepoints as per standard of care; (5) oxygen saturation via pulse oximetry were measured—timepoints as per standard of care, recorded at intervals indicated by clinical concern; (6) administration of oxygen; (7) administration of manual resuscitation or ventilate (bag-valve-mask ventilation); (8) administration of airway adjunct (nasopharyngeal or oropharyngeal airway); (9) administration of naloxone (yes or no); (10) cardiopulmonary resuscitation; and (11) ambulance called.

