Research personnel will record basic information (day or time and drug reported for injection) for each participant’s SIF attendance. Site research personnel will record the time of self-injecting by monitoring participants from a distance and estimating the time of drug injection (this may include multiple injections within a single episode). If this is not possible to record, the site personnel will document that it could not be collected. Site research personnel will also record event interventions for an acute or overdose event (as applicable), including start time, end time, event assessment or level of intervention, clinicians’ unique ID, and overdose criteria. A record of “no acute event” will also be maintained if the self-injecting visit occurred without any requirement for site personnel intervention. Any adverse events will also be recorded and, if necessary, an early withdrawal form will be completed if the participant did not progress to use the biosensor at visit 1 and declined further participation.

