##### Algorithm Under Test

The PneumoWave Hub receives and transmits biosensor data to a cloud storage facility. The stored data are then processed in the cloud using experimental algorithms for the presence of reduced chest movement events in adults.

The performance of the algorithm under test will be compared to the reference events at the SIF in terms of the AUT’s sensitivity and false alarm rate. If the target numbers for sample size, injecting visits, and acute events are not reached, the analysis will still be possible and feasible.

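### The comparator labelled safe is really visits without a staff-identified event, not visits shown to be free of respiratory depression, and the article's two definitions of an event disagree

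*Protocol article*

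**What the plan says.** **Groups compared.** Under Primary Outcome Measures, group 1 is "those experiencing hypoxia and meeting defined criteria for an acute or opioid overdose" and group 2 is "those not experiencing symptoms of hypoxia or acute or opioid overdose (ie, safe injecting event".

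**Data at every injecting event.** Under SIF-Determined Outcome Measures, the only respiratory item collected at every injecting event is "any apnea and prompts to breathe".

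**Data at acute events only.** A separate list opens with "The outcome measures that will be collected for each acute event (including prompts), as applicable". It contains respiratory rate, which starts after the first clinical indication of overdose, and the saturation item "oxygen saturation via pulse oximetry were measured", taken at standard-of-care timepoints.

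**How a visit becomes a non-event.** Visit 1 Procedures keeps a record of no acute event "if the self-injecting visit occurred without any requirement for site personnel intervention". The section on visit 2 onwards repeats this.

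**Reference and performance.** Reference Event counts anything that required staff intervention, from an audio stimulus to an ambulance call, and admits that some of these may not have been overdoses. Algorithm Under Test then judges the algorithm against these events by its "sensitivity and false alarm rate".

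**Stated need.** The Introduction says the research needs a setting in which both the presence and the absence of overdose can be verified from outside the device.

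**The concern.** Presence of an event is examined clinically; absence is inferred from the lack of intervention. The label safe, and the aim in the Abstract of separating opioid-induced respiratory depression from non-fatal use, both reach further than that inference.

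Two things are at stake. First, visits with depression that staff did not notice or act on enter the comparator. There they count against the algorithm if it alarms, they are invisible if it does not, and they are used in development as examples of harmless breathing. Second, the primary outcome and the biosensor analysis do not sort visits in the same way, so sensitivity depends on which section the analyst follows.

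**Working it through.** **Step 1. Place each kind of visit under both definitions.**

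| Visit | Primary Outcome Measures | Reference Event and Algorithm Under Test |
|---|---|---|
| Overdose with hypoxia | Group 1 | Reference event |
| Staff prompt, no hypoxia | Neither: group 1 requires hypoxia, group 2 excludes acute events | Reference event (acute) |
| Apnea recorded, no intervention | Not settled | Non-event; an alarm is false |
| Depression not noticed by staff | Group 2 in practice | Non-event; an alarm is false, a miss is not counted |
| No depression, no intervention | Group 2 | Non-event |

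The second row is a contradiction between sections. The third and fourth rows show that the comparator is defined by staff action.

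**Step 2. Size of the comparator.** Inputs from Sample Size: 4,000 visits in total, an event rate of 1.2%, and a target of about 40 events. The plan's own figure is not exactly reproduced: 4,000 × 0.012 = 48. The difference does not matter here.

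- With 48 events: 4,000 − 48 = 3,952 non-event visits.
- With 40 events: 4,000 − 40 = 3,960 non-event visits.

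The visits already recorded (1,145, with 10 overdose events) are not a usable base, because the number of other acute events is not reported.

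**Step 3. Illustration of mislabelled visits and false alarms.** Let u be the share of S = 3,960 non-event visits with unrecognised depression, s the probability that the algorithm flags such a visit, and f its false alarm rate per visit truly without depression. None of the three is in the article. Assume s = 0.90 throughout.

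Apparent false alarm rate = f(1 − u) + s·u. Its excess over f is u(s − f), which is positive whenever s > f. The share of counted false alarms that are correct detections is s·u divided by the apparent rate.

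| u (assumed) | Mislabelled visits, u × 3,960 | f = 1%: apparent rate (share correct) | f = 5%: apparent rate (share correct) |
|---|---|---|---|
| 0.5% | 20 | 1.445% (31%) | 5.425% (8%) |
| 1% | 40 | 1.89% (48%) | 5.85% (15%) |
| 2% | 79 | 2.78% (65%) | 6.70% (27%) |
| 5% | 198 | 5.45% (83%) | 9.25% (49%) |

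For u = 1% and f = 1%: 0.01 × 0.99 + 0.90 × 0.01 = 0.0189. With the 3,952 base, 1% is 39.5 visits instead of 39.6.

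**Step 4. Direction for sensitivity.** Let D be reference events with depression, N reference events without it, and U the unrecognised episodes. Write d for detection in D and g for the alarm probability in N.

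- Reported: (d·D + g·N) / (D + N).
- For all depression: (d·D + s·U) / (D + U).

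If N = 0 and s < d, the reported figure is too high. If U = 0 and g < d, it is too low. The article gives none of N, U, s or g, so the net sign cannot be determined.

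**The case against.** The strongest reply is that the article is open about its reference. The Abstract, the Objectives, Study Design, Reference Event and Algorithm Under Test all name staff-identified or staff-measured outcomes as the comparator. Group 2 is worded by symptoms of hypoxia, so a reader who infers a claim of measured normal saturation goes beyond the text. This stands: the fault lies in the label safe and in conclusions about respiratory depression, not in concealment of the reference.

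The threshold for an acute event is also low. Prompts already count, so visits with a prompt to breathe are already outside the non-event group. This stands too, and it narrows the problem to episodes that supervising staff neither noticed nor acted on.

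Third, against the target of an event needing intervention, an alarm on mild depression is a false alarm by design. That is coherent for staff-recognised events, but it does not support statements about respiratory depression as such.

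Fourth, the parenthesis attached to group 1 equates it with an acute event, so the gap for prompted visits may be loose drafting. It remains a conflict, because the same sentence requires hypoxia.

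A reader might also infer that the false alarm rate is an upper bound, or that sensitivity must be overstated. Neither is assured. Alarms in acute events without depression are credited as hits and leave the false alarm count, and a correctly silent algorithm in such events is scored as a miss.

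**Conclusion.** The concern holds as a mismatch between what the comparator is called and what is observed, together with a conflict between sections over prompted visits without hypoxia. Both are fixed by the article's own text and are not details left to an analysis plan. Sensitivity and false alarm rate, as defined, describe agreement with staff recognition.

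The size of any distortion is unknown. The figure of about 40 mislabelled visits rests on an assumed 1% rate, and the false alarm figures also rest on an assumed 90% detection of unrecognised episodes. They show only that a rare mislabel could equal the whole target event set. If such episodes are flagged more often than truly clean visits, they raise the apparent false alarm rate. The net effect on sensitivity could go either way.

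It might be inferred that the study needs oximetry at every visit. The documents do not require that conclusion: this is an observational pilot that leaves standard of care unchanged, and the point can be met by wording and tabulation.

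**What to change.** 1. In Primary Outcome Measures, define group 2 as visits with no staff-identified event and drop the word safe. Make group 1 consistent with Reference Event, so that a prompted visit without hypoxia has one stated place.
2. Report sensitivity separately for overdose events and for other acute events.
3. Use the apnea item already collected at every visit: take visits with recorded apnea but no intervention out of the clean comparator and tabulate them on their own.
4. In Algorithm Under Test, state that sensitivity and false alarm rate are relative to staff recognition, and that alarms in visits without intervention are unverified. Do not present the false alarm rate as a guaranteed upper bound.

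The cost is some rewording, one extra tabulation from data already collected, and a slightly weaker claim. No oximetry or other procedure is added and clinical care is untouched. The article describes data analysis as ongoing.
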